**Methods:**

Forty adult women (index participants) who have recently screened for CC will be recruited, 20 of whom will be randomly assigned to take part in the intervention and 20 to the wait-list control. Each index participant will be asked to recruit up to three female social network members (i.e., alters; maximum total = 120 alters) who have not screened for CC to participate in the study. Assessments (survey and chart abstraction) will be administered at baseline and month 6 to index and alter participants. The primary outcome is CC screening among participating alters, with a secondary outcome being engagement in CC prevention advocacy among index participants. Repeated-measure multivariable regression analyses will be conducted to compare outcomes between the intervention and control arms.

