## Methods

### Study design

This study will pilot test a social network-based group intervention that aims to empower and mobilize women who have been screened for CC to advocate for CC screening and treatment in female members of their social network (referred to as “alters”). We will pilot the intervention in a randomized controlled trial of 40 women who have been screened for CC (referred to as index participants), with 20 randomly assigned to receive the intervention (in two groups of 10) and 20 to the wait-list control [(each evenly stratified by age (under and over age 35) and history of CC-related treatment)]. Individual randomization entails risks for contamination, but statistical models suggest that ≥ 30% of the control arm must receive the equivalent of a full-strength intervention to result in meaningful contamination [24]. We opted for the wait-list control rather than an attention control, because this provides clearer findings for policy makers when considering intervention effects, and adequate control for attention may not be feasible given the 2-h duration and group dynamics of the workshops. The control arm receives the intervention after the completion of month-6 follow-up assessments. There is no way to blind the participants on whether or not they receive the intervention; this could potentially influence the outcomes, as clients may feel more or less incentivized to perform well in light of whether or not they receive the intervention. We do not see a way to prevent this potential bias, nor a way to distinguish such effects from actual intervention effects, but this limitation will be cited in reports of study findings. Data will be collected at baseline and month 6 from index participants and up to three alters of each index participant (max. total = 120 alters) who have not previously screened for CC. The primary outcome is alter CC screening over the 6-month follow-up period; secondary outcomes are index participant reported engagement in CC screening advocacy, internalized CC stigma, and disclosure of CC screening experience.

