The adapted intervention consists of 7 workshops. *Workshop 1* focuses on *addressing fears and concerns related to CC risk and use of self-compassion and peer support to overcome these fears*, as well as introducing the overall vision for empowering women to become change agents for CC prevention and treatment. With participants feeling more supported, *Workshop 2* focuses on *building skills and decision-making for sharing one’s personal CC screening experience*, knowing to whom to disclose and when and how to initiate and navigate disclosure and conversations about CC. *Workshop 3* builds skills and motivation for *healthy living* so that their own behavior (e.g., good nutrition, periodic VIA screens) is consistent with the behavior they encourage in others, as well as learning facts and myths related to CC to facilitate accurate CC screening advocacy. *Workshop 4* introduces the concept of a social network and how one’s network can serve as a tool for CC prevention advocacy and dissemination of CC-related information. *Workshops 5 and 6* focus on the skills needed for successful *CC-related advocacy*, including strategies for how to start conversations about CC and to keep these discussions going, as well as learning effective communication skills (e.g., reflective listening, paraphrasing, open-ended questions). *Workshop 7* inspires a *commitment to ongoing CC advocacy* through peer solidarity and support. The workshops will be conducted using a structured facilitator manual, in the predominant local languages of Samia and Lusoga, by two trained women from Namayingo who have experience being screened for CC. Using principles of compassion-focused therapy [27], the workshops will be administered in a group format to facilitate the use of *sharing of experiences* to build support, solidarity, and motivation among participants; *group problem-solving* and *role playing* to build skills and self-efficacy; *setting personal goals* regarding healthy living, disclosure, and advocacy; and homework to reinforce practice of new skills and generate personal experiences to be processed in the workshops. The seven workshops will be conducted weekly over 2 months, and each workshop will last 2 h. Participants will receive 30,000 Uganda shillings (~US $8) for attending each workshop to cover transport costs.

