***Secondary outcomes***	
Receipt of CC-related treatment (e.g., thermal therapy; chemotherapy; radiation), if warranted: index and alter	Self-report; chart abstraction
Healthy living behaviors (condom use, diet, alcohol use, CC rescreening): index and alter	Developed in-house
Engagement/receipt of CC prevention and treatment advocacy: index and alter	Developed in-house

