#### Social network assessment

Using Network Canvas software, each index participant will list 12 female adult alters (which is adequate to capture structural and compositional variability) [32] with whom they interact most. For each alter, we will gather information to assess *network composition* (e.g., age, HIV status, relation to index; perceived history with CC screening and treatment; knowledge of index’s CC screening and treatment). Index participants will report how well each alter knows each other alter to assess *network structure* (e.g., density or connectedness among alters). *To assess CC advocacy*, we will ask the index participant if they have encouraged the alter regarding CC screening and/or treatment, risk reduction behaviors (condom use), and any perceived resulting action (e.g., alter sought VIA screening). At follow-up, we will determine whether listed alters are the same or unique from those listed at baseline, which allows for both sequential cross-sectional analyses and longitudinal analyses of alter data. Our prior research shows that alter behaviors such as diagnosis disclosure and health-seeking behaviors can be accurately reported by index participants [33].

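### Advocacy is defined by the report of unblinded, trained index women and the bias is called inseparable, although the alter reports listed in Table 1 can partly check it

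*Protocol article*

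**What the plan says.** All references are to the protocol article.

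- **Outcome definition.** Study design states that "secondary outcomes are index participant reported engagement in CC screening advocacy", then adds internalized stigma and disclosure. The Methods paragraph of the abstract names only advocacy, "with a secondary outcome being engagement in CC prevention advocacy among index participants".
- **Measurement.** Under Social network assessment, the index woman lists 12 female contacts, and for each of them "we will ask the index participant if they have encouraged the alter regarding CC screening and/or treatment".
- **Second reporter.** Table 1, under secondary outcomes, lists "Engagement/receipt of CC prevention and treatment advocacy: index and alter", on an instrument developed in-house.
- **Blinding.** Study design says "There is no way to blind the participants on whether or not they receive the intervention" and then "We do not see a way to prevent this potential bias, nor a way to distinguish such effects from actual intervention effects". It promises to cite the limitation in reports.
- **Training.** Under Intervention, Workshops 5 and 6 "focus on the skills needed for successful" advocacy, participants set personal advocacy goals, and Workshop 7 seeks a continuing commitment to it. Controls receive the workshops only after the month-6 assessment.
- **Verification.** Under Measures, chart abstraction covers screening and treatment. It does not cover advocacy.

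**The concern.** The women who report the advocacy outcome know their arm. In one arm only, they have practised the behaviour, set goals for it and pledged to continue it. Over-reporting that differs between arms is therefore foreseeable, and nothing in the outcome definition under Study design guards against it. The accuracy evidence cited under Social network assessment concerns index women's reports of their alters' behaviour. It does not concern reports of the woman's own advocacy.

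Advocacy is the step through which the intervention is meant to raise alter screening. The Statistical analysis section also treats it as a potential mediator, to be related to treatment condition and to the primary outcome. If only reporting changes, the pilot could pass on to the larger trial a signal that the mechanism works when it does not. Study design treats the problem as insoluble, yet Table 1 already plans a second informant on the same behaviour.

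**Working it through.** **1. The plan's own figure.** None is stated for advocacy. The Sample size section concerns alter screening: 120 × 0.9 / 2 = 54 per arm, and 54 / (1 + 2 × 0.01) = 52.9, which agrees with the stated 53. Nothing below depends on it.

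**2. The passages side by side.**

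| Place | Who reports advocacy |
|---|---|
| Abstract, Methods | Not stated; engagement located in index women |
| Study design | Index woman |
| Social network assessment | Index woman, contact by contact |
| Table 1, secondary outcomes | Index (engagement) and alter (receipt) |
| Statistical analysis | Index-alter comparison not mentioned |

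Because the index woman answers for each named contact, her answer about an enrolled alter can be set against that alter's own answer. Lack of blinding can act in two ways:

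- *Behaviour*: women advocate more or less because they know their arm. Alter report cannot separate this from an intervention effect.
- *Reporting*: women claim advocacy that did not happen. Alter report bears directly on this.

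The statement that there is no "nor a way to distinguish such effects from actual intervention effects" is sound for the first and too broad for the second.

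**3. Illustration at pair level (rates assumed).** Let a share p of alters be truly encouraged in both arms, and let intervention women also claim a share o of those not encouraged. The index-reported rate is then p + o(1 − p).

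- p = 0.40, o = 0.10: 0.40 + 0.10 × 0.60 = 0.46
- p = 0.40, o = 0.30: 0.40 + 0.30 × 0.60 = 0.58

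The false difference against 40% in control is 6 to 18 points. If alters answered without error, they would show 40% in both arms. They would confirm 0.40 / 0.46 = 87% down to 0.40 / 0.58 = 69% of intervention women's claims, against all of the controls' claims. Agreement by arm would expose that pattern.

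**4. Illustration at woman level (bias assumed).** There are 20 index women per arm, no true effect, two-sided alpha .05 and b = over-reporting in SD units. The rejection rate is 1 − Φ(1.96 − b√(20/2)) + Φ(−1.96 − b√(20/2)).

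| b | Rejection rate |
|---|---|
| 0 | 5% |
| 0.2 | 9.7% |
| 0.4 | 24% |
| 0.6 | 48% |
| 0.8 | 72% |

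For a yes/no outcome, by exact enumeration of the pooled z-test:

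| True rate, both arms | Share of intervention non-advocates who claim advocacy | Observed rate, intervention | Rejection rate |
|---|---|---|---|
| 30% | 0 | 30% | 5.3% |
| 30% | 20% | 44% | 15% |
| 30% | 30% | 51% | 26% |
| 30% | 40% | 58% | 41% |
| 50% | 0 | 50% | 4.3% |
| 50% | 20% | 60% | 9% |
| 50% | 30% | 65% | 15% |
| 50% | 40% | 70% | 25% |

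For scale, 20 per arm detects d = (1.960 + 0.842) × √(2/20) = 0.89 with 80% power.

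**5. Reach of the check.** At most 3 of 12 listed contacts (25%) have a second report. That is at most 20 × 3 = 60 pairs per arm, or 54 after the plan's assumed 10% attrition.

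**The case against.** **Table 1 already handles part of this.** Alter-reported receipt is itself listed under secondary outcomes. A reader might infer that the whole plan rests on self-report. It does not: only the abstract and Study design place the outcome with index women alone. This objection stands and reduces the point to a reconciliation plus a check.

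**The blinding sentence may concern behaviour only.** It speaks of women being more or less motivated to do well, which most naturally means conduct. That is a fair reading. But the sentence is about influence on outcomes generally, and the outcome defined a few lines later is a self-report, so the limit should be explicit.

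**Agreement statistics can be left to a SAP.** True, and their absence is not counted as a fault here. The point is what the article fixes: the reporter, and the claim that nothing can be distinguished.

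**Alter report should not replace index report.** A reader might infer that it should become the defining measure. The documents do not support that. Enrolled alters are selected: they already know the index woman's screening experience, and she is comfortable asking them. The intervention aims at the wider network. Alters may learn her arm. In both arms the index woman calls them to describe the study, and alters could count that call as encouragement, which would shrink a true difference. Table 1 does not show whether the alter item identifies who gave the advocacy.

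**Advocacy is one unranked secondary outcome in a pilot.** A reader might call it the key secondary because the abstract names no other. The documents do not rank it, and the primary outcome is checked against charts. This too stands.

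**Conclusion.** The point holds in limited form. Study design defines advocacy by the report of unblinded women, trained and asked to commit in one arm only, and treats any resulting bias as indistinguishable. Table 1 plans an alter report that can partly check the reporting component, so the two places should be reconciled.

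The size of any bias cannot be known from the documents. The 6 to 18 points and the rejection rates above show only what the stated assumptions imply. A reader might infer that over-reporting will produce a false result here; the documents do not support that, only that the design as described would not reveal it. The reasoning assumes that alters' answers are less affected by arm than index women's, which is plausible because they attend no workshops, but unproven. This is a worthwhile, cheap improvement to a secondary outcome. It does not put the chart-verified primary outcome in question.

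**What to change.** 1. In Study design and the abstract, state that advocacy is assessed by both reporters, as Table 1 lists.
2. Keep index report across the 12 listed contacts, since only it covers the wider network. Present the arm comparison of alter-reported receipt beside it.
3. Report index-alter agreement by arm for enrolled pairs.
4. Conclude that advocacy increased only if the two sources are consistent.
5. Limit the no-way-to-distinguish statement to effects on behaviour, and say that the reporting effect is partly checked by alter report.
6. Confirm that the alter item names the index woman as the source and excludes her recruitment call.

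**Cost.** This needs wording changes and one further table, with no extra visits or participants. If the in-house alter item does not identify the source, it needs rewording or one added question. The remaining limits should be reported: at most three selected contacts per woman, alters who may know the arm, and agreement estimated from at most 60 pairs per arm.

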#### Sample size

The small sample limits statistical power, but our goal is to assess the preliminary effect size and other parameters to inform a future larger trial. Assuming 120 alters enroll, attrition rate of 10% among alters (we have retained 90–94% over 12 months in past studies in Uganda) [25, 26], *ICC* = .01 to control for clustering within the alters of each participant, and a 5% rate of receiving CC screening in control alters, the effective sample size will be 53 per arm, enabling us to detect a medium effect size (Cohen’s *d* = 0.57; 19 percentage point difference in CC screening among alters during the 6-month follow-up period), with 80% power (alpha = .05). If ICC is as high as .05, and as few as 80 alters enroll, the detectable effect size = 0.72 (25.5 percentage point difference between groups).

### Setting

The study will take place in Namayingo, a rural community in the Busoga region of Uganda, and specifically Buyinja and Banda health centers. In addition to CC screening and thermal therapy that takes place at the two health centers, Rays of Hope Hospice Jinja (RHHJ) conducts 1- to 3-day CC screening “camps” in Namayingo, during which it provides free or low-cost VIA screening and thermal therapy, as well as referrals and assistance to access more invasive CC treatment. Women screened in the RHHJ camps are registered in a database used to track them and facilitate further follow-up and outreach. However, these camps did not take place in the study setting during the course of the 6-month follow-up period.

With support from the leadership and community volunteers of the Buyinja and Banda health centers, as well as RHHJ and African Palliative Care Association, we composed a community advisory board consisting of members of key stakeholder groups (district health officials, community leaders, reproductive health providers, and women living with CC risk). This board provided key input into the development and adaptation of the intervention and instrumentation and will hold half-day meetings at key junctures throughout the implementation of the trial to inform the need for any adjustments to the intervention, as well as interpretation and dissemination of findings.

### Participants

Women are eligible to enroll as index participants if they are age 18 years or older, have screened for CC within the past year, have stable health status (i.e., not in end stages of disease), and shared their CC screening experience with at least one alter who is perceived to not have screened for CC in the past 3 years. Alter participants are eligible if they are at least 18 years of age, are recruited by an index participant, and report never being screened for CC.

Index participants will be recruited through the RHHJ database of women who have received CC screening and referral from Buyinja and Banda providers who have screened women for CC. An RHHJ staff member or health center provider will inform eligible women of the study, and those who express interest in participating will be referred to the study coordinator for formal eligibility screening and implementation of consent procedures. Women who provide written informed consent will then be administered the baseline assessment and be randomly assigned to the intervention or control arm. To recruit alters, we will use data collected from the baseline survey assessment of female social network members to randomly select 5 alters who know the participant’s CC screening experience (or as many as there are if < 5) and ask the participant if she is comfortable asking 3 of these alters to participate. The index participant will be asked to call each selected alter at the end of the interview to describe the study in the presence of the coordinator, who will schedule a study visit for alters who express interest in participating. If an alter refuses or cannot be reached, a replacement will be randomly selected from the list of alters who know the index participant’s CC screening experience.

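### As narrated, index women are randomised before their alters are enrolled, and nothing withholds allocation until then, so differential recruitment of the women who carry the primary outcome is not excluded

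*Protocol article*

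**What the plan says.** In the Participants section, index women who consent "will then be administered the baseline assessment and be randomly assigned to the intervention or control arm". The text then turns to alters. The team will "randomly select 5 alters who know the participant’s CC screening experience", using the network data from the baseline survey, and "ask the participant if she is comfortable asking 3 of these alters to participate". Next, "The index participant will be asked to call each selected alter at the end of the interview to describe the study", with the coordinator present, "who will schedule a study visit for alters who express interest in participating". After a refusal or failed contact, "a replacement will be randomly selected from the list of alters".

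The Methods paragraph of the abstract uses the same order. It gives the 20:20 assignment first, and then: "Each index participant will be asked to recruit up to three female social network members".

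The Study design section names alter screening over six months as the primary outcome and states: "There is no way to blind the participants on whether or not they receive the intervention". It acknowledges that knowing the arm may affect how participants perform. It does not mention an effect on which alters enter the study.

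**The concern.** Randomising index women balances index women. It balances alters too only if the set of enrolled alters cannot depend on the arm. If an index woman knows whether she will be trained as an advocate or must wait, she may differ in whom she is willing to ask, how she puts the request, or how many alters she brings in. Alters may also respond differently to what they are told. Any resulting difference in the alters' underlying readiness to be screened enters the primary comparison directly and looks the same as an intervention effect.

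This matters in a pilot as well. The Sample size section says that the purpose is to obtain a preliminary effect size and other parameters for a larger trial, so a distorted estimate would carry over into that trial's design.

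**Working it through.** **1. Order of steps, as far as the text fixes it.**

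| Step | Before allocation is known? |
|---|---|
| Index consent, baseline survey, network list | Yes |
| Random draw of 5 candidates | Open: uses baseline data, but the time of the draw is not given |
| Index woman says which 3 she is comfortable asking | Open |
| Calls at the end of the interview | Open: before assignment if this is the baseline session and assignment follows it |
| Contact with replacements | Open: may be later, for women who could not be reached |
| Alter's visit and enrolment | After the call; narrated after assignment, with nothing placing it before |

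No sentence withholds allocation until the last row is complete.

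**2. Room for selection.** The Sample size section plans for 120 alters, or as few as 80. With 40 index women that is 120/40 = 3, or 80/40 = 2, alters each. In the lower scenario, (120 − 80)/120 = one third of the possible alters are not enrolled. That shortfall could differ by arm in number or in kind.

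**3. Whether the planned analysis would correct it.**
- Intent-to-treat keeps enrolled alters in the arm of their index woman. It does not change who enrolled.
- Attrition weights and item imputation deal with losses after entry.
- Alters must report never having been screened, so the baseline outcome is 0 for all of them. The time-by-arm term therefore has no baseline difference to remove.
- Adjustment for alter characteristics covers only what is measured, and receptivity to screening may not be.

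**4. The plan's own figures.** Inputs from the Sample size section: 120 alters, 10% attrition, ICC 0.01, 3 alters per index woman, 5% control rate, 80% power, alpha 0.05 (taken as two-sided).
- Effective n per arm = (120 × 0.9 / 2) / [1 + (3 − 1) × 0.01] = 54 / 1.02 = 52.9, stated as 53.
- Power for 5% v 24% at 53 per arm (pooled z-test) = 0.802, stated as 80%.
- Arcsine effect size for 5% v 24% = 0.573, stated as 0.57.

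The figures reproduce, and the order of recruitment does not alter them.

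**5. Illustration of the stakes.** The shifted rates are assumptions and do not come from the document. Suppose there is no intervention effect, but selection alone gives one arm a rate of 5% + b against 5%. Let p̄ be the mean of the two rates, with

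SE₀ = √[2p̄(1 − p̄)/53] and SE₁ = √{[p₁(1 − p₁) + p₂(1 − p₂)]/53}.

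The two-sided rejection probability is Φ[(b − 1.96·SE₀)/SE₁] + Φ[(−b − 1.96·SE₀)/SE₁].

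| Assumed rates | SE₀ | SE₁ | Rejection probability | b as share of 19 points |
|---|---|---|---|---|
| 5% v 8% | 0.0479 | 0.0478 | 0.091 + 0.005 = 0.096 | 3/19 = 16% |
| 5% v 10% | 0.0512 | 0.0509 | 0.162 + 0.002 = 0.163 | 5/19 = 26% |
| 5% v 15% | 0.0583 | 0.0575 | 0.402 + 0.000 = 0.402 | 10/19 = 53% |

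Exact binomial enumeration of the same test at 53 per arm gives about 9%, 15% and 41%.

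**The case against.** A reader might infer that alters are chosen, called and enrolled with knowledge of the arm, in front of an unblinded coordinator. The document does not support that. The only interview just described is the baseline assessment, so selection and the first calls may well come before assignment. The coordinator is never said to know the arm. The blinding sentence concerns participants' awareness of whether they receive the intervention, not what is known during the calls.

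The plan also has real safeguards: a random draw of candidates from a list collected at baseline, calls made in the coordinator's presence, random replacement, and one eligibility rule for all alters. Workshops run in groups of ten, so little or no training need have been given when alters are called. Recruitment of network members is to be reported, though not explicitly by arm. Finally, this is a pilot, and nothing in the document supports the assumed shifts or says which arm they would favour. A 10-point shift would triple the 5% control rate through selection alone.

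All of that stands, and it limits the point. It does not remove it. Alters enrol at a visit scheduled after the call, replacements may be contacted later still, and discretion remains at the asking, the description and the agreement to attend. It could be said that a condensed article leaves the timing of concealment to the full protocol. But this article does give an order, twice, and that order puts assignment first.

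**Conclusion.** The point holds as a risk that the stated design leaves open, not as demonstrated bias. As narrated, assignment comes before alter recruitment, and nothing keeps allocation from the index woman or the coordinator until alters are enrolled. Differential recruitment of the units that carry the primary outcome is therefore not excluded, and the planned analysis would not correct it.

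Size and direction are unknown; bias could favour either arm. The false-positive rates of roughly 10%, 16% and 40% rest entirely on assumed selection shifts of 3, 5 and 10 points. They show how sensitive the comparison is and do not estimate what will happen. The sample size figures are unaffected.

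**What to change.** State the order explicitly in the Participants section. Complete the index baseline; select and call the alters; obtain their consent, confirm eligibility and take their baselines, or exhaust the candidate list; only then generate the index woman's allocation or reveal it to her and the coordinator. Align the abstract with this order. Keep the random draw and the random replacement.

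The cost is a change of wording or an amendment, and a short delay between index baseline and allocation. The delay should matter little, because intervention women must in any case wait for a group of ten to form. The sample size does not change.

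The Setting section already refers to the follow-up period in the past tense, so recruitment may be complete. If it followed the narrated order, report by arm the numbers of alters named, approached, refused and enrolled, with the baseline characteristics of those enrolled. Add differential alter recruitment to the blinding limitation in the Study design section.
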